#### Control communities

In control communities, CHW will not be trained to administer RDT and AL to pregnant women. The women will be mainly followed through their attendance to the health facilities at the ANC.

#### At time of delivery for all communities

The final study visit will occur at the time of delivery. A blood sample will be collected just before delivery for haemoglobin measurement as well for detection of malaria infection and SP resistance markers and a short data collection form on their current health status will be administered. A placenta biopsy will be collected and all newborns will be physically examined and weighed as soon as possible after birth (Figures 1 and 2). Gestational age will be estimated using the Ballard Score [24]. For women not delivering at a health facility, study staff will follow them up at home and will collect the same information and biological samples as at the health facilities as soon as possible.

### Randomisation

The allocation of the two trial arms will be carried out separately but consistently for each country. Prior to the trial start, maps and population size of the study site in all three countries will be obtained. CHWs who work in villages with a population size of approximately 1,000 to 2,000 will be identified. If more clusters than required are identified, the appropriate number of representative clusters will be selected at random. Distance from the centre of each village to the nearest IPTp-SP-providing health facility will be calculated and used to group the clusters into three categories. Stratification by these categories will ensure that the villages with the larger distances are evenly distributed between trial arms. The balanced allocation of each cluster to a trial arm will be done using a computer-based randomisation (StataCorp LP, USA, http://www.stata.com).

### Clinical data collection and patient treatments

#### At the antenatal clinic

All study participants returning to the ANC for scheduled or unscheduled visits will undergo a health assessment by study staff. In case of suspected malaria (fever, headache, and so forth), a RDT test will be performed and, if positive, AL administered.

#### Community health worker home visits in the intervention arm only

RDT will be performed on a monthly basis for women enrolled in the intervention arm regardless of the presence of malaria symptoms. If positive for malaria, treatment will be given with AL. If the woman is severely ill at time of visit (from malaria or other causes and/or from complications from the pregnancy) she will be referred to the health facility for further care.

### Laboratory evaluations

#### Haematology

Maternal haemoglobin will be measured using Hb301 Hemocue*®* (part of the Radiometer Group, Sweden) and anaemia (haemoglobin <11 g/dL) diagnosed at the time of delivery.

#### Peripheral malaria infection

Blood samples will be collected by finger pricks at specified time points during the trial for blood slides (thick blood film) and blood spots on filter paper. Thick blood smears will be stained with 3% Giemsa for 30 minutes and read by trained microscopists at each site. Parasite densities will be calculated by counting the number of asexual parasites per 200 leukocytes (or per 500 leukocytes if the count is <10 asexual parasites/200 leukocytes), assuming a leukocyte count of 8,000/μl. A blood smear will be considered negative when the examination of 100 high-power fields does not reveal asexual parasites. Each slide will be read separately by two experienced microscopists and discrepancies resolved by a third reader.

Blood spots on filter paper will be used for the molecular diagnosis of *P. falciparum* (to detect sub-patent infections) and the identification of SP resistance markers.

#### Placental malaria

A 1 cm^2^ biopsy specimen will be obtained from the maternal-facing side of the placenta as soon as possible after delivery. Biopsy specimens will be preserved in 10% neutral buffered formalin which will be processed and embedded in paraffin wax by standard techniques. Pending histological evaluation, all biopsies will be kept at 4°C. Paraffin sections 4 millimeters thick will be stained with hematoxylin-eosin stain.

Placental biopsies will be classified according to the following definitions [25]:Acute infection (parasites present, malaria pigment absent)Chronic infection (parasites and malaria pigment present)Past infection (no parasites but pigment present)No infection (both parasites and malaria pigment absent)

### Safety considerations

The risk of participating in this cluster randomized trial is low. The World Health Organization recommends the use of artemisinin-based combination therapy, in this case AL, during the second and third trimester of pregnancy [26, 27]. The subjects will not be exposed to any danger or increased risk due to the conduct of the study. There is the possibility of mild discomfort and bruising at the site where blood is obtained. Collection of blood samples is part of the normal procedure in the diagnosis of malaria and is considered not to be a medical risk when adequately performed by a qualified health worker (including CHWs). Placental biopsies will be obtained after delivery, with no risk or discomfort for the neonate or mother. Qualified personnel using appropriate disposable equipment will collect blood samples and placental biopsies.

CHWs in the intervention arm will be trained on safety reporting requirements and on the recognition of danger signs and serious adverse events (SAEs). In case of any SAE of the pregnant woman, deterioration of her condition or reaction after the administration of the drug, the CHW will report this immediately to the study staff who will perform the necessary further assessments and referrals to the appropriate health facilities if required.

During the course of the study, any important medical events which occur will be appropriately recorded, managed and reported. Midwives and/or research staff will record all occurrences of adverse pregnancy outcomes such as a miscarriage or spontaneous abortion (<28 weeks of gestation), stillbirth (>28 weeks) or the occurrence of any congenital malformation. All reported SAEs and important medical events will be reported to the study site investigator or deputy. The local principal investigator will inform the sponsor and the coordinating investigator. The sponsor will inform the ethics committee and the Data Safety and Monitoring Board.

### Study endpoints

#### Primary endpoint

Prevalence of placental malaria (any category, including past infection) determined by a placental biopsy taken soon after delivery at a health facility.

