**Methods/design:**

This is a multi-centre cluster-randomised controlled trial involving three countries with varying malaria endemicity; low (The Gambia) versus high transmission (Burkina Faso and Benin), and varying degrees of SP resistance (high in Benin and moderate in Gambia and Burkina Faso). CHW and their related catchment population who are randomised into the intervention arm will receive specific training on community-based case management of malaria in pregnancy. All women in both study arms will be enrolled at their first ANC visits in their second trimester where they will receive their first dose of IPTp-SP. Thereafter, CHW in the intervention arm will perform scheduled monthly screening and treatment in the womens homes. At time of delivery, a placental biopsy will be collected from all women to determine placental malaria. At each contact point, filter paper and blood slides will be collected for detection of malaria infection and SP resistance markers.

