#### Intervention communities

CHWs allocated to the intervention arm will follow specific training on community-based case management of malaria, the need for monthly testing of pregnant women using a rapid diagnostic test (RDT), and on issues related to malaria in pregnancy, including the benefit of IPTp-SP and administering SP as early as possible in the second trimester of pregnancy.

The CHWs will continuously identify all pregnant women in their own catchment area, visit eligible women in their home and encourage them to attend the ANC as early as possible in their pregnancy for enrolment. The CHW will check after a week if the ANC was visited. For women who do not attend the ANC, the CHW will further encourage and discuss reasons for non-attendance.Thereafter, at monthly intervals up to the last week of gestation, the CHW will revisit the study participant’s house (Figure 2). The CHW will collect a blood slide and a blood spot on filter paper, perform a RDT and administer a full course of AL to any woman with a positive RDT. In case of treatment, the CHWs will return to assess uptake and compliance by administering a short questionnaire and checking the empty packaging of the treatment at the end of the course.

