### Analytical plan

Appropriate summary statistics (that is, mean and standard deviation for normally distributed variables and median and inter-quartile range for non-normally distributed variables) will be used to describe the baseline data.

The primary analysis will compare the prevalence of placental malaria (defined as number of positive samples by total number of samples) between the intervention and the control group.

Secondary analysis will compare the following variables between trial arms: (i) mean haemoglobin levels and prevalence of anaemia (haemoglobin <11 g/dL) at delivery, (ii) prevalence of *P. falciparum* peripheral infection (microscopy and PCR) at delivery and during pregnancy, (iii) mean birth weight and proportion of newborns with low birth weight (<2,500 g) between the two trial arms, (iv) level of ANC attendance by village/cluster and coverage of IPTp-SP (defined by number of doses completed during pregnancy), and (v) SP resistance markers profiles.

For the primary and secondary analysis both linear regression (for continuous outcomes such as haemoglobin levels) and logistic regression (for binary outcomes such as placental malaria) will be used to quantify the difference between trial arms. The regression models will allow for the multi-level structure of the data (that is, individuals within villages) using random effects and for all relevant co-variates to be taken into account. Model assumptions will be checked to confirm reliable estimates.

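### The primary endpoint is tied to facility deliveries, while the sampling, denominator and sample-size sections count all women

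*Protocol article*

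**What the plan says.** The Primary endpoint section of the protocol article defines placental malaria (any category, including past infection) as "determined by a placental biopsy taken soon after delivery at a health facility". Whether the place qualifies the delivery or the biopsy, a sample taken at home falls outside it.

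Four other places describe a wider population:

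- Abstract, Methods/design: "At time of delivery, a placental biopsy will be collected from all women to determine placental malaria".
- At time of delivery for all communities: where a woman does not deliver at a facility, "study staff will follow them up at home and will collect the same information and biological samples as at the health facilities".
- Analytical plan: the primary comparison is of "prevalence of placental malaria (defined as number of positive samples by total number of samples"), with no restriction by place.
- Sample size rationale: at least 60 women enrolled per cluster and 5,400 in total, with no deduction for home deliveries.

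**The concern.** Two denominators for the primary outcome stand in the same document, and nothing in it says which prevails. An analyst could defend either one, including after seeing the data.

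The narrower denominator is the less safe of the two. Place of delivery is settled after randomisation. In the intervention arm only, community health workers visit eligible women and "encourage them to attend the ANC as early as possible in their pregnancy for enrolment", check a week later whether they went, and then return monthly until the last week of gestation. ANC attendance is itself a secondary outcome. Some spill-over to place of delivery is plausible. The Discussion links limited facility access to distance, poverty and low education, so women who deliver at home may also differ in malaria risk. If both hold, restricting to facility births compares groups that randomisation did not create. Even if neither holds, the restriction reduces the number of women analysed per cluster below the planning figure.

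**Working it through.** **1. Reproducing the plan's figure.** Inputs from the Sample size rationale: p0 = 0.15, p1 = 0.105, coefficient of variation k = 0.15, m = 60 women per cluster, 10% significance, 80% power. Sidedness is not stated; two-sided is used here. The Hayes–Bennett formula for unmatched clusters is

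c = 1 + (z_α/2 + z_β)² × [p0(1−p0)/m + p1(1−p1)/m + k²(p0² + p1²)] / (p0 − p1)²

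- Binomial terms: 0.1275/60 + 0.093975/60 = 0.003691
- Between-cluster term: 0.0225 × (0.0225 + 0.011025) = 0.000754
- Sum divided by 0.045² = 0.004446 / 0.002025 = 2.195
- (1.645 + 0.842)² = 6.183
- c = 1 + 6.183 × 2.195 = 14.57, rounded up to 15

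Power with 15 clusters per arm = Φ(√(14/2.195) − 1.645) = 81.1%. The total is 2 × 45 × 60 = 5,400. Both agree with the plan when all 60 women per cluster contribute.

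A second route also gives 15.0 clusters: m = 40 with a one-sided 10% test. On that reading, power stays at about 80% until the facility share falls to 40/60 = 67%.

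**2. Power if only facility births count.** The facility-delivery share is not in the documents, so it is assumed. With m = 60 × share, prevalences as planned and two-sided 10%:

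| Assumed facility share | m | Women analysed | Per-country power | Clusters per arm needed for 80% |
|---|---|---|---|---|
| 100% | 60 | 5,400 | 81.1% | 14.57 |
| 90% | 54 | 4,860 | 78.0% | 15.83 |
| 80% | 48 | 4,320 | 74.3% | 17.39 |
| 70% | 42 | 3,780 | 70.0% | 19.40 |
| 60% | 36 | 3,240 | 64.8% | 22.09 |
| 50% | 30 | 2,700 | 58.8% | 25.84 |

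**3. Possible selection effect (illustration; every input except the 0.70 is assumed).** Suppose prevalence without intervention is 12% in women who would deliver at a facility anyway and 19.5% in the others. Facility delivery is 60% in control and 75% in intervention.

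- Overall: 0.60 × 0.12 + 0.40 × 0.195 = 0.15, the planning value
- Control, facility births only: 0.12
- Intervention, facility births only, no true effect: (0.60 × 0.12 + 0.15 × 0.195)/0.75 = 0.135
- Apparent risk ratio under no effect: 0.135/0.12 = 1.125
- With the planned true risk ratio of 0.70: 0.70 × 1.125 = 0.79

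Two other assumed settings give 0.74 (13% and 18% prevalence; 60% versus 70% facility births) and 0.81 (12% and 19.5%; 60% versus 80%). In all three the shift is towards the null. If the share and the kind of woman delivering at a facility are the same in both arms, the multiplier is 1 and there is no bias from this source.

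**The case against.** The best defence is that no passage actually excludes home samples. The exclusion is inferred from one phrase, which may only describe the usual setting, since all women are encouraged to deliver at a facility. The abstract, the delivery procedures, the analytical plan and the sample size all point to every sample being used. This stands: the point is a contradiction, and data are lost only if the definition is applied literally.

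The bias mechanism can also be challenged. Community health workers are described as promoting ANC attendance, not facility delivery. Encouragement to deliver at a facility goes to both arms, and randomisation is stratified by distance to the nearest facility. A reader might infer that the intervention shifts place of delivery and so breaks the randomised comparison. The documents do not establish this; they make it possible.

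A reader might also infer that the restriction removes the hard-to-reach women the trial is meant to serve. That goes too far. Enrolment is in principle at the first ANC visit, with village-level consent only for non-attenders, so the document does not equate enrolled home deliverers with that group.

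Finally, the power loss is per country. The analytical plan does not confine the primary comparison to one country. With 45 clusters per arm and m = 36, the same formula gives about 95% power even at two-sided 5%, assuming the same prevalences and k in all countries. This also stands, but the Sample size rationale claims 80% power within each site, and that is the claim affected.

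**Conclusion.** The concern holds as an internal contradiction in the population of the primary endpoint. The definition names facility deliveries; the sampling, the denominator and the sample size describe all women.

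The consequences are conditional on applying the definition as written. Per-country power would then fall from 81% to between 78% and 59% over an assumed facility share of 90% to 50%, below the stated 80%. This takes a two-sided 10% test; on a one-sided reading the shortfall begins only below a share of about 67%. Bias arises only if facility share or case mix differs between arms. Its size and direction cannot be fixed from the documents, and the 0.79 in place of 0.70 is an illustration. In that illustration the error hides benefit rather than creating it. The documents do not support the stronger statements that home biopsies are definitely discarded or that the comparison is definitely biased.

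**What to change.** In the Primary endpoint section, delete the closing health-facility qualifier, so that the endpoint is placental malaria on a biopsy taken as soon as possible after delivery, wherever that occurs. This agrees with the abstract, the delivery procedures and the analytical plan. Analyse all enrolled women with a biopsy according to their cluster's allocation. Report place of delivery and biopsy availability by arm. Keep facility births only as a sensitivity analysis.

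The cost is one phrase plus two descriptive tabulations, since home sampling is already planned. The downside is small: home placentas may be sampled later and give poorer histology, which the sensitivity analysis would help to show. Recruitment was ongoing when the article was submitted, so the change should be made before outcome data are compared by arm.

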#### Secondary endpoints

Maternal anaemia (haemoglobin <11 g/dL) at deliveryMaternal *P. falciparum* peripheral infection (microscopy and PCR) at delivery and during pregnancyLow birth weight (<2,500 grams)IPTp-SP coverage by village/clusterSP resistance markers profilesNumber of ANC visits during pregnancyNumber of doses of IPTp-SP taken during pregnancy

### Sample size rationale

The study will test the primary hypothesis that CSST plus IPTp-SP will reduce placenta malaria compared to IPTp-SP alone. Sample size calculation was performed according to Hayes and Bennett [28]. Based on available data, the prevalence of placental malaria (any category, including past infection) is at least 15% in the three study sites. Although the coefficient of variation for placental malaria is not known, it is set at 0.15 within each country. It is assumed that the intervention will decrease placental malaria by 30%, from 15% to 10.5%. Furthermore, the assumption is made that each CHW will recruit at least 40 pregnant women per year, corresponding roughly to a population of 800 people (assuming 5% of the population is pregnant). Within each study site, the study will be able to show a significant difference between intervention and control groups with 15 clusters per arm at 80% power and at the 10% significance level. This translates to 45 clusters per arm across the three study sites. Therefore, the total study population will be 5,400 women, 1,800 women in each country, and will require an 18-month recruitment period in order to enrol at least 60 women per cluster.

### Data handling and record keeping

All data handling and record keeping will be standardised across the three study sites. At the health facility, all pregnant women will be recorded on a study register held at each clinic. Women who are enrolled onto the study will also be given a unique identity number.

A standardised data collection form on the health status, medical history of the women, and socio-demographic characteristics will be administered by health staff at the time of enrolment at the health facility. A standardised data collection form on current health status will then be administered at subsequent ANC visits (intervention and control arm) and at each monthly visit by the CHWs in the intervention arm only. All data will be double entered using OpenClinica® (http://www.openclinica.com) databases at each site. Consistency checks will be performed and any outliers and missing data points will be checked against the original forms and subsequently amended in the dataset. Errors including missing data that may have occurred during the data collection will be reported with a minimum delay for further investigation.

All names and addresses will be removed from the data collection forms before data entry. The datasets will be password protected and only accessed by the data manager and local investigators at each study site. All samples will be labelled with the woman’s unique identity number and date of collection. This will ensure anonymity so all handlers of the specimens are blinded to the intervention allocation.

### Analytical plan

Appropriate summary statistics (that is, mean and standard deviation for normally distributed variables and median and inter-quartile range for non-normally distributed variables) will be used to describe the baseline data.

The primary analysis will compare the prevalence of placental malaria (defined as number of positive samples by total number of samples) between the intervention and the control group.

Secondary analysis will compare the following variables between trial arms: (i) mean haemoglobin levels and prevalence of anaemia (haemoglobin <11 g/dL) at delivery, (ii) prevalence of *P. falciparum* peripheral infection (microscopy and PCR) at delivery and during pregnancy, (iii) mean birth weight and proportion of newborns with low birth weight (<2,500 g) between the two trial arms, (iv) level of ANC attendance by village/cluster and coverage of IPTp-SP (defined by number of doses completed during pregnancy), and (v) SP resistance markers profiles.

For the primary and secondary analysis both linear regression (for continuous outcomes such as haemoglobin levels) and logistic regression (for binary outcomes such as placental malaria) will be used to quantify the difference between trial arms. The regression models will allow for the multi-level structure of the data (that is, individuals within villages) using random effects and for all relevant co-variates to be taken into account. Model assumptions will be checked to confirm reliable estimates.

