## Methods/designs

### Study areas and participant eligibility

This is a multi-centre trial involving three countries with varying malaria endemicity: low (The Gambia) versus high transmission (Burkina Faso and Benin), and varying degrees of SP resistance (high in Benin [19] and moderate in Gambia and Burkina Faso [20]). This will ensure that the study outcomes would be broadly generalisable in order to facilitate the formulation of recommendations for both the West African region and other sub-Saharan countries. The Gambia, a country where malaria transmission has decreased to levels thought not possible a few years ago (and hence in a so-called “epidemiological transition”), will provide information possibly applicable to countries that may reach a similar status in the (near) future.

In The Gambia, the study is situated in the eastern part of the country on the southern bank of the Upper River Region (about 170,000 inhabitants). It will be centred around the Basse Health Centre and satellite health facilities. This is an area of seasonal malaria transmission (July-December) that has recently experienced a significant decline in malaria infections. Nevertheless, malaria remains a significant problem with about 15% of pregnant women with placental malaria at delivery as detected by histopathology [9].

In Burkina Faso, the study is situated in the centre-west of the country in the Nanoro health district catchment area (about 145,000 inhabitants). Malaria transmission is high and extremely seasonal and overlaps with the rainy season (June-October).

In Benin, the study is situated at the Atlantic Region in the southern part of the country, in the Glo-Djigbé, Zinvié and Zè district communities (about 136,000 inhabitants). Malaria transmission is perennial and the main burden of the disease occurs during the two rainy seasons (April-July and October-November).

The current treatment policy of uncomplicated malaria in pregnancy is oral quinine but artemisinin-based combination therapy (artemether-lumefantrine (AL)) may be used in the second and third trimester of pregnancy for all three countries, or amodiaquine-artesunate in Burkina Faso and Benin [21–23].

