In this study, it is proposed to add an “extension” strategy to the communities in rural areas to the standard IPTp-SP delivered through the health facilities and thus bring health services closer to where women live. The study will build on the use of CHWs who are already managing malaria cases within the framework of CCMm [18]. At this level, RDTs for the diagnosis of malaria are already being used or their implementation is planned. CCMm supported by RDT is at various stages of implementation; in The Gambia, the National Malaria Control Program is planning to introduce nationwide CCMm supported by RDT; in Burkina Faso, CCMm has been implemented and is currently managed by an international non-government organisation (Plan International) and four local non-government organisations under the supervision of the National Malaria Control Program; in Benin, CCMm is part of the National Malaria Policy, though it still needs to be scaled up nationwide.

The study will extend the CCMm which at present is primarily aimed at children under the age of 5 years to pregnant women. The aim is to improve both IPTp-SP coverage as CHWs encourage women to attend the ANC for the IPTp at the right time, allow systematic screening for malaria infection and provide an opportunity to treat malaria when the prophylactic effect of IPTp-SP has waned. The trial will also investigate the prevalence of SP resistance markers in the positive malaria samples obtained during the study as it could be hypothesized that the beneficial effects of the intervention might be more pronounced in areas with high SP resistance, because women could be more prone to placental malaria when IPTp-SP has a reduced effect and, although not yet observed in West Africa, extremely high levels of SP resistance markers in the parasite population may even lead to adverse effects of SP [34].

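### Clusters are randomised and the trial is sized country by country, but the stated analysis names neither country nor any site-level result

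*Protocol article*

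**What the plan says.** Four places in the protocol article give country a role.

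- **Study areas and participant eligibility** describes the design: "This is a multi-centre trial involving three countries with varying malaria endemicity: low (The Gambia) versus high transmission (Burkina Faso and Benin"), with high SP resistance in Benin and moderate resistance elsewhere. The reason given is generalisability: "This will ensure that the study outcomes would be broadly generalisable in order to facilitate the formulation of recommendations". The Gambia in particular "will provide information possibly applicable to countries that may reach a similar status in the (near) future".
- **Randomisation** says that allocation is carried out separately for each country.
- **Sample size rationale** states one overall hypothesis ("The study will test the primary hypothesis that CSST plus IPTp-SP will reduce placenta malaria compared to IPTp-SP alone") but bases the numbers on single sites: "Within each study site, the study will be able to show a significant difference between intervention and control groups" with 15 clusters per arm, 80% power and a 10% significance level. The totals of 45 clusters per arm and 5,400 women are three times the single-site figures.
- **Discussion** links the resistance-marker work to a conjecture that "the beneficial effects of the intervention might be more pronounced in areas with high SP resistance".

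The **Analytical plan** then states: "The primary analysis will compare the prevalence of placental malaria" between intervention and control. It uses logistic regression with random effects for individuals within villages and allows for relevant covariates, which it does not list. Resistance markers appear only as a secondary variable compared between arms.

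**The concern.** The stated model matches neither the randomisation nor the sizing. Country is the level at which allocation was done separately, yet the only structure named is women within villages. The sample size exists to support a comparison in each site, yet no site-level estimate is named.

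Two things follow. First, if country is left out, differences in prevalence between countries fall into the village random effect and widen the interval for the pooled effect. Second, a reader who wants to know what the result means for a setting like The Gambia, which the protocol itself raises, has no planned estimate to turn to. Including country as a covariate solves the first problem but not the second, because adjustment assumes one common effect. Country comparisons added once results are known would be post hoc.

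**Working it through.** **1. Reproducing the plan's figure.** Inputs from the Sample size rationale: p0 = 0.15, p1 = 0.105, k = 0.15, m = 60 women per cluster, 10% significance level (taken as two-sided; the article does not say), 80% power. Hayes and Bennett, unmatched:

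c = 1 + (z_α + z_β)² × [p0(1−p0)/m + p1(1−p1)/m + k²(p0² + p1²)] / (p0 − p1)²

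= 1 + (1.645 + 0.842)² × [0.002125 + 0.001566 + 0.000754] / 0.045² = 1 + 6.183 × 0.004446 / 0.002025 = 14.57, so 15 clusters per arm.

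Power with 15: SE = √(0.004446/14) = 0.01782; 0.045/0.01782 = 2.525; Φ(2.525 − 1.645) = 0.81. Then 3 × 15 = 45 per arm and 90 × 60 = 5,400 women. The stated figures reproduce as a single-site calculation. (One-sided 10% with m = 40 also gives 15.0.) The pooled comparison, with 45 per arm, has over 99% power under the same inputs.

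**2. What leaving country out would cost.** The article says only that prevalence is at least 15% in the three sites, so the spread is an assumption: 15% in one country and P in the other two, with a 30% reduction everywhere. Within-country variance of a cluster prevalence is p(1−p)/60 + 0.15²p². Between-country variance is (difference)² × (1/3)(2/3). Summing over arms:

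| P | within | between | SE ratio = √[(within + between)/within] |
|---|---|---|---|
| 25% | 0.003898 + 0.002668 = 0.006566 | (0.10² + 0.07²) × 0.2222 = 0.003311 | √1.504 = 1.23 |
| 40% | 0.005944 + 0.004021 = 0.009965 | (0.25² + 0.175²) × 0.2222 = 0.020694 | √3.077 = 1.75 |

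At equal prevalence the ratio is 1. The cost is a wider interval rather than a lost test: at P = 40% the pooled difference is 0.3 × 0.3167 = 0.095, the unadjusted SE is √(0.030659/44) = 0.0264, and power at two-sided 5% is still Φ(3.60 − 1.96) = 0.95.

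**3. What site estimates would look like.** On the log risk ratio scale at 15% control prevalence, the site variance is [0.0944 + 0.1421 + 2 × 0.0225]/14, so SE = 0.142. At a true risk ratio of 0.70 the expected 95% interval is about 0.53 to 0.92.

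**4. What an arm-by-country contrast could detect.** For one country against the other two, SE = √(0.142² + 0.142²/2) = 0.174. The ratio of risk ratios detectable with 80% power is exp(−2.80 × 0.174) = 0.61 at two-sided 5%, or 0.65 at two-sided 10%. Recomputing the SE for each pair of assumed risk ratios (two-sided 5%, 14 to 15 effective clusters per arm per site):

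| One country v other two | Power |
|---|---|
| 0.6 v 0.8 | 37–39% |
| 0.5 v 0.7 | 44–46% |
| 0.5 v 0.8 | 72–75% |
| 1.0 v 0.55 | 94–96% |

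These are single contrasts. An overall test across three countries has two degrees of freedom and somewhat less power against the same patterns.

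**The case against.** The strongest reply is that this is a condensed analysis section and that centre terms and heterogeneity tests are usually left to the analysis plan. Country could be among the covariates, and nothing excludes by-country reporting; separate randomisation and per-site sizing even suggest that it is intended. That has weight: silence is not prohibition, so the point cannot be that the trial is unable to look at country. What stands is a mismatch between sections of one document. The sample size is justified by a within-site comparison that the analysis does not name, and the only data structure named omits the level at which allocation was separate.

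Two stronger readings are tempting and not supported.

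- A reader might infer that the three countries were chosen to test whether the intervention works differently by transmission or SP resistance. The stated reason is generalisability, no objective concerns effect modification, and the resistance idea appears only as a conjecture in the Discussion.
- A reader might infer that settings will be compared by which sites reach significance. That would be a poor method: with an identical effect everywhere, all three sites reach significance in only about 0.81³ = 53% of trials. But no section proposes it, and the Sample size rationale says only what each site can show.

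It is also true that a pooled ratio can hide a null site: risk ratios of 1.0, 0.55 and 0.55 average to 0.70 at equal control prevalence. This is a possibility, not a prediction; the plan assumes the same reduction everywhere.

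**Conclusion.** The point holds as an inconsistency between sections. Randomisation and sizing are by country, and the stated analysis is not. The overall test is not endangered, since pooled power is ample. What is at stake is precision if country is omitted (SE larger by a factor of about 1.2 to 1.75 under the assumed prevalence spreads, none if prevalences are equal) and the absence of named site results that the trial was sized to provide. An arm-by-country test would be informative only about large differences. It could not attribute a difference to SP resistance, because only Benin is described as having high resistance and only The Gambia as having low transmission, so each is confounded with everything else about that country. The power figures rest on k = 0.15, 60 women per cluster and 15% control prevalence in every country. The change is worth making because it costs almost nothing.

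**What to change.** In the Analytical plan:

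- include country as a fixed effect in the placental malaria model;
- report the three country-specific effects with confidence intervals alongside the pooled effect;
- pre-specify one arm-by-country test as a secondary analysis, naming its scale and significance level;
- state that differences between countries will be judged by that test, described as differences between settings and not as an effect of SP resistance, and that a non-significant result will not be read as equal effects.

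The cost is analysis wording and a few model terms, with no new data. The downside is one more secondary test with limited power: about 80% only for a ratio of risk ratios near 0.6, and under 50% for 0.5 v 0.7. The wording should be fixed before results by arm are seen.
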